#### Research questions and hypotheses

The primary purpose of the trial is to test the independent and synergistic efficacy of the 12-week sports-oriented exercise referral intervention and the self-help web-based intervention intended to promote sustained and increased levels of physical activity over a period of 12 months. Do these interventions separately and in combination improve these indicators and do they improve them above that expected by existing gym-based GP referral alone? The secondary questions are whether these interventions improve other clinical indicators of cardiovascular health (for example, body mass index, waist and hip measures, blood pressure and other measures that contribute to the QRisk2 risk indicator) above that expected by existing gym-based GP referral? Do these interventions increase participation in sporting activity over a period of 12 months?

The interventions individually will be regarded as successful if they lead to an average increase in activity of 100 metabolic equivalent of task (MET)-minutes per week. This equates to engaging in an extra moderate intensity activity, say brisk walking (3.3 MET) for 30 minutes per week. The new interventions will be regarded as superior to the standard gym-based referral if they increase activity levels above those of the standard care gym-based exercise by 20 MET-minutes per week.

We will assess changes in indicators relating to cardiovascular health including blood pressure, weight, and waist and hip circumference. In terms of blood pressure, the interventions will be regarded as successful if they lead to an average decrease in blood pressure of 2.5 mmHg. We will assess the proportion of the sample reducing their blood pressure by more than 10 mmHg and an intervention will be regarded as a success if more than 20% of the members of that study arm achieve a reduction greater than this. The interventions will also be deemed to have been successful in promoting sports participation if they increase sports-related activity by 100 MET-minutes per week.

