## Methods/design

Participants will be inactive people aged 18 to 74 years who are eligible to be referred by their GPs for an exercise intervention. Participants will be people with hypertension or high-normal blood pressure and assessed as being inactive or moderately inactive using the General Practice Physical Activity Questionnaire (GPPAQ) screening tool. The inclusion and exclusion criteria are detailed below.

The study will be conducted in the Guildford and Waverley CCG area (Surrey, UK) and patients will be recruited via GP surgeries serving catchment areas within reasonable reach of Surrey Sports Park and the five DC leisure centres in Waverley, Surrey, UK. We have designed the study with the intention to allow recruitment for all patients eligible for an exercise referral within the 9 months of the proposed trial data collection phase.

The trial design is shown in Figure 1. The key features are that, after a patient has been assessed as likely to benefit from an exercise intervention, their referral is to the project research assistant who will allocate the patient to one of four conditions on the basis of previous independent randomisation. These are: 1) GP gym-based referral (GPGR, the treatment as usual control); 2) GP gym-based referral plus web tool (GPGR + WEB); 3) sport referral at Surrey Sports Park (SPR); and 4) sport referral at Surrey Sports Park plus web tool (SPR + WEB). After obtaining informed consent patients attend a 12-week exercise programme (sport or gym) and their activity levels and sporting participation are monitored again at 6 months and 12 months after starting the exercise programme. Pending ethical approval the intention is to commence recruitment in the early autumn of 2013 for a period of 9 months.

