### Measures

PA will be assessed via an online questionnaire using the short-form version of the International Physical Activity Questionnaire
[29], which is a well validated measure of physical activity in a number of domains and permits the calculation of MET per minute values for activities in each domain, including leisure and sporting activity
[30]. As recent research has shown that the International Physical Activity Questionnaire can overestimate activity in sedentary individuals we will use a second validated self-report measure, the Self-Report Walking and Exercise Tables
[31] that also permits the estimation of MET minutes. We will include additional items to tap the types of sporting activity people do.

Participants will complete the GPPAQ screening tool at the beginning and end of the study for inclusion on their patient records.

Health indicators will include measures of height and weight (body mass index (BMI)), waist and hip circumference, and blood pressure. These measures will be assessed by the exercise professional at the beginning, middle and end of the 12-week exercise programme. They will be collected again at the end of the 12-month period on visiting their GP surgery. Patients will be asked to consent to the collection of their most recent blood sugar, cholesterol/high-density lipoprotein ratio and indications of whether they are receiving treatment for high blood pressure. We will ask for access to medical records to assess whether they have chronic kidney disease, diabetes, rheumatoid arthritis or atrial fibrillation. These indicators are required for the QRisk2 calculations. To assess safety we will also monitor well-being during the period of the exercise programmes. Blood pressure measurements will be taken by the research team and/or by specially trained exercise professionals using Omron M6W blood pressure monitors (Omron Health Care Co. Ltd, [name]).

General health will be assessed with the RAND SF36
[32] along with short measures of drinking (the AUDIT
[33]) and smoking behaviour (The Fagerstrom Test
[34]). These will be assessed at baseline and at 12 month follow-up.

Intervention exposure will be assessed by attendance at the exercise programme sessions. Web-tool usage will be assessed by number and duration of logins over the study period.

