#### Intervention effectiveness

For the primary outcome of activity, and assuming normal variable distributions, the intervention arms will be compared to the control arm using *t*-tests and one-way analysis of covariance using study arm as the between-subjects factor and baseline activity scores as the covariate (following Senn,
[36]). Similar analyses will be conducted for the secondary outcome variables and in all cases effect sizes reported. Where variable distributions do not initially permit the use of parametric inference tests, variables will be subjected to mathematical transformation to achieve normality. In cases where transformations are not effective, non-parametric tests on difference scores will be used. Differences between arms in the proportions achieving more than 10 mmHg reductions in blood pressure will be assessed using chi-square tests.

Analyses will be conducted on a per-protocol basis. Interim assessment of the efficacy of the interventions will be made at 6 months.

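### Blood pressure and body measures are taken at the exercise programme at baseline but at the GP surgery at 12 months, which leaves the uncontrolled within-arm blood pressure criteria open to a measurement shift

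*Protocol article*

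**What the plan says.** Three sentences under Measures in the protocol article govern these outcomes.

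- Programme period, for height, weight, waist, hip and blood pressure: "These measures will be assessed by the exercise professional at the beginning, middle and end of the 12-week exercise programme".
- Twelve months, for the same measures: "They will be collected again at the end of the 12-month period on visiting their GP surgery".
- Blood pressure, with no visit specified: "Blood pressure measurements will be taken by the research team and/or by specially trained exercise professionals using Omron M6W blood pressure monitors".

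Methods/design describes allocation by the research assistant on referral, with the programme following, so a reading at the start of the programme is post-allocation. The section on sample size and randomisation blinds only the primary analyst.

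Research questions and hypotheses sets two blood pressure rules. The first is "the interventions will be regarded as successful if they lead to an average decrease in blood pressure of 2.5 mmHg". The second counts participants who fall by more than 10 mmHg: "an intervention will be regarded as a success if more than 20% of the members of that study arm achieve a reduction greater than this". Intervention effectiveness plans t-tests and "one-way analysis of covariance using study arm as the between-subjects factor and baseline activity scores as the covariate" for activity, similar analyses for secondary outcomes, and chi-square tests on the 10 mmHg responders.

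**The concern.** The reading that serves as baseline is taken in an exercise setting by the person supervising the programme, who necessarily knows sport from gym. The 12-month reading is taken in a GP surgery by someone the article does not identify. The blood pressure sentence lists the research team and exercise professionals but no surgery staff. Either trial personnel attend the surgeries, which is not stated, or the 12-month reading departs from that sentence. For weight, waist and hip, no 12-month assessor is named.

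Any systematic difference between the two settings becomes part of each participant's change. The responder rule refers explicitly to members of a single arm, and the mean-fall rule names no comparator. Neither has a control to remove such a difference, so an arm could be called successful, or a real fall could be missed, because of where and by whom blood pressure was read.

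A second route concerns sport versus gym only. Because baseline is read after allocation by staff who know the programme, randomisation does not protect it. If baseline error differed between the two programmes, a shared 12-month setting would not remove the difference.

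**Working it through.** **Inputs from the protocol article**
- Sample size section: systolic SMD 0.27 equated with 3.8 mmHg; diastolic 0.17 with 2.1 mmHg; planned effect 0.125 SD; 500 per arm.
- Research questions and hypotheses: thresholds of 2.5 mmHg, 10 mmHg and 20%.

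**Assumptions (the article gives no values)**
- The size of any measurement shift.
- The correlation ρ between baseline and 12 months: 0.5 to 0.8.
- The slope of 12-month on baseline values: 0.4 to 0.6.
- Normal distributions with equal SD at both visits.
- The success rules apply at 12 months. The article does not name the visit for them.

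The article gives no figure for measurement shift, so there is none to reproduce. Its one design figure covering mmHg, 80% power at 500 per arm and 0.125 SD, recomputes to 50.7%. That is a separate matter and nothing below depends on it.

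**1. Scale.** Systolic SD = 3.8 / 0.27 = 14.1 mmHg, so the planned effect is 0.125 × 14.07 = 1.76 mmHg. Diastolic SD = 2.1 / 0.17 = 12.4 mmHg.

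**2. Mean-fall rule.** Observed mean change = true change + shift. With no true change and surgery readings 2.5 mmHg lower, the observed fall is 2.5 mmHg and the rule is met.

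**3. Responder rule.** SD of change = SD × √(2(1 − ρ)). At ρ = 0.7 the systolic value is 14.07 × √0.6 = 10.9 mmHg. With no true change:
- no shift: P(Z > 10 / 10.9) = 17.9%
- surgery 2.5 mmHg lower: P(Z > 7.5 / 10.9) = 24.6%
- surgery 2.5 mmHg higher: P(Z > 12.5 / 10.9) = 12.6%

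| Systolic, no true change | No shift | 2.5 lower | 5 lower |
|---|---|---|---|
| ρ = 0.5 | 23.9% | 29.7% | 36.1% |
| ρ = 0.7 | 17.9% | 24.6% | 32.3% |
| ρ = 0.8 | 13.1% | 20.0% | 28.7% |

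At ρ = 0.5 the 20% line is passed with no shift at all. For diastolic pressure at ρ = 0.7, a 2.5 mmHg shift moves the share from 14.8% to 21.7%.

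**4. Between arms, common shift.** The shift enters both arm means and subtracts out: bias 0 mmHg.

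**5. Sport versus gym, baseline error differing by δ.**
- Comparison of 12-month values alone: bias 0.
- Change scores: bias δ, so 1 to 2 mmHg for δ = 1 to 2 mmHg.
- ANCOVA: bias = slope × δ, from 0.4 × 1 = 0.4 to 0.6 × 2 = 1.2 mmHg. Relative to 1.76 mmHg this is 23% to 68%. With equal SDs the slope equals ρ, so at 0.7 the range is 0.7 to 1.4 mmHg.
- Type I error for change scores with SD of change 14.1 (ρ = 0.5): SE = 14.07 × √(2/500) = 0.89 mmHg. A 1 mmHg differential raises the two-sided 5% level to about 20%, and a 1.76 mmHg differential to about 51%.

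**The case against.** The strongest reply is that the three Measures sentences can be read together without conflict. A surgery is a place, not an assessor. Research staff could measure there, and the Omron M6W is named without restriction to programme visits. A single 12-month setting away from the intervention staff is itself a strength, and a condensed article may leave staffing to the full protocol.

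Much of this stands, and it limits what may be concluded. A reader might infer a change of device; the text does not show one for blood pressure, and it names no instrument for weight or girths at any visit. A reader might infer a definite change of blood pressure assessor; that is possible, not established. A reader might also take it that every arm is measured at its own venue. Sport referral is placed at Surrey Sports Park, but the gym venue is not assigned: the leisure centres appear only in the description of the catchment, "within reasonable reach of Surrey Sports Park and the five DC leisure centres in Waverley, Surrey, UK".

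The reply does not dispose of the change of setting, or of the post-allocation baseline read by programme staff. The article states both, so they are not details left out. Nor does it answer the within-arm rules, where even a shift identical in all arms is not removed.

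**Conclusion.** The point holds for the within-arm blood pressure criteria. A 2.5 mmHg shift from setting alone meets the mean-fall rule with no treatment effect and, at SD 14.1 mmHg and ρ = 0.7, carries the responder share from 17.9% past 20% to 24.6%. A shift the other way would hide a real fall. The shift size and the correlation are assumptions; the article supports the SD and the thresholds.

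A reader might go further and conclude that the randomised blood pressure comparisons are confounded by the switch. The article does not support that. A common shift cancels between arms. Sport versus gym is biased only if baseline error differs by programme, which is plausible because staff know the programme but is not shown. With an assumed differential of 1 to 2 mmHg and a slope of 0.4 to 0.6, the ANCOVA bias is 0.4 to 1.2 mmHg against a planned effect of about 1.8 mmHg. Web versus no-web contrasts compare arms with the same programme type and are little exposed.

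Change to the end of the 12-week programme uses the exercise professional at both visits and does not carry the setting switch. All these outcomes are secondary, and the primary outcome, the online activity questionnaire, is unaffected. The change should be made, but the primary analysis does not depend on it.

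**What to change.** 1. Reconcile the three Measures sentences. Name one assessor type for the outcome baseline and the 12-month readings (for example the research team, already listed), the same Omron M6W and the same written procedure and, where feasible, the same setting in all four arms. Do the same for weight, waist and hip.
2. Take the outcome baseline after consent and before allocation is revealed. A surgery reading at referral is not a ready-made answer: the article does not state an in-person referral visit, and a reading then could precede consent.
3. Keep the exercise professional's readings for programme monitoring only.
4. Rest blood pressure conclusions on between-arm contrasts, and report the 2.5 mmHg and 20% within-arm figures descriptively.

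The cost is protocol wording, some scheduling and staff time, and monitors at the chosen site. The research assistant cannot be blinded, so another team member would be preferable for the 12-month readings if available.

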**Trial design diagram.**

The inclusion criteria are as follows:The patient is aged 18 to 74 years at randomisation.The patient has been diagnosed as having hypertension or high-normal blood pressure as recorded on their GP records and is regarded by their GP as someone who would benefit from attending an exercise programme. High-normal blood pressure is defined as systolic blood pressure 130 to 139 mmHg or diastolic blood pressure 85 to 89 mmHg based on clinical records.The patient is screened as being ‘inactive’ or ‘moderately inactive’ on the GPPAQ.The patient has access to the internet and an email account.The patient is able to understand the Informed Consent Form, and understand study procedures.The patient has signed the Informed Consent Form.

The exclusion criteria are as follows:The patient is pregnant.Inability to freely consent to take part in the studyInability to understand the study materials.The patient is unable to access the internet/emailCurrent participation in another clinical trial relating to physical activity or exerciseAny condition that, in the GPs opinion, compromises the subject’s ability to meet protocol requirements or to complete the study.The patient is referred out of the trial by the exercise professional on the grounds that the programme is, in their judgement, likely to cause harm.

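### Blood pressure success is judged within each arm with no record of drug changes, so a fall from a started or increased antihypertensive counts as intervention success

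*Protocol article*

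**What the plan says.** Research questions and hypotheses sets two blood pressure criteria. The first concerns the mean: "the interventions will be regarded as successful if they lead to an average decrease in blood pressure of 2.5 mmHg". The second counts responders, that is, patients whose pressure drops by over 10 mmHg, and applies to each arm on its own: "an intervention will be regarded as a success if more than 20% of the members of that study arm achieve a reduction greater than this". Both are judged inside an arm. Neither names a comparator, a time point, or systolic or diastolic pressure.

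The inclusion criteria (Methods/design) admit a patient "diagnosed as having hypertension or high-normal blood pressure as recorded on their GP records". No criterion concerns antihypertensive treatment or its stability.

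Under Measures, blood pressure is "assessed by the exercise professional at the beginning, middle and end of the 12-week exercise programme", and again at 12 months at the GP surgery. Participants are asked to consent to "indications of whether they are receiving treatment for high blood pressure", which the section groups with the inputs needed for QRisk2. Nothing says that this item is repeated or that it captures drug, dose or change.

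Intervention effectiveness specifies t-tests and analysis of covariance on baseline, with similar analyses for secondary outcomes. For responders it says: "Differences between arms in the proportions achieving more than 10 mmHg reductions in blood pressure will be assessed using chi-square tests". No treatment information enters these analyses, and treatment is not among the moderators or mediators named in the next section.

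**The concern.** Participants have a condition that their GP may treat with drugs, and follow-up lasts a year. Drugs may be started, increased, reduced or stopped in that time. Under the two success rules, a patient who gains nothing from exercise but falls by more than 10 mmHg on a new drug is a responder. A patient who improves enough for treatment to be cut back may be a non-responder.

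Because the rules have no comparator, randomisation does not protect them: drug-related falls common to all four arms still count as success in each arm.

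The between-arm tests are a separate matter. They are distorted as measures of the exercise effect only if treatment changes differ by arm, for example if the less effective arm receives more added drugs and its deficit is hidden.

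This is a data question before it is an analysis question. A yes/no indication cannot show a dose increase in someone already treated, and no analysis plan can later separate changes that were not recorded.

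**Working it through.** The protocol gives no figure for drug changes or their effect, so there is no stated result to reproduce on this point. The following is an illustration.

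**Inputs from the protocol (Sample size and power calculations)**
- Systolic SMD 0.27, equated to 3.8 mmHg, so the implied SD is 3.8/0.27 = 14.1 mmHg.
- Design effect size 0.125, so 0.125 × 14.1 = 1.76 mmHg. It serves here only as a yardstick. The power statement attached to it is a separate matter.
- 500 participants per arm.

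**Assumptions (not in the protocol)**
- No exercise effect, and normally distributed change.
- Baseline to follow-up correlation ρ of 0.5 to 0.7.
- A drug start or increase lowers pressure by D = 9 mmHg (range 5 to 10).
- A share q of the arm has such a change.

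**Responder rule (20% line)**

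SD of change = 14.1 × √(2(1 − ρ)). Share falling by more than 10 mmHg = (1 − q) × [1 − Φ(10/SD)] + q × [1 − Φ((10 − D)/SD)].

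For ρ = 0.7, the SD of change is 10.9:
- No drug change: 1 − Φ(10/10.9) = 0.179.
- Among those with a change: 1 − Φ(1/10.9) = 0.464.
- With q = 10%: 0.9 × 0.179 + 0.1 × 0.464 = 0.208.

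| ρ | SD of change | q = 0 | q = 10%, D = 5 | q = 10%, D = 9 | q = 10%, D = 10 |
|---|---|---|---|---|---|
| 0.7 | 10.9 | 17.9% | 19.4% | 20.8% | 21.2% |
| 0.6 | 12.6 | 21.3% | 22.7% | 23.9% | 24.2% |
| 0.5 | 14.1 | 23.9% | 25.1% | 26.2% | 26.5% |

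Drug changes in 10% of the arm carry it over the line only at ρ = 0.7, and there not when D = 5. At ρ = 0.6 or 0.5 the line is passed with neither drugs nor exercise.

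**Mean rule (2.5 mmHg)**

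Mean fall due to drugs = q × D. With D = 9 and q = 10%, this is 0.9 mmHg. Reaching 2.5 mmHg through drugs alone needs q = 2.5/9 = 28%; over D = 5 to 10 the requirement runs from 50% down to 25%.

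**Between arms**

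Shift in the contrast = (difference in q) × D. A 10-point difference gives 0.10 × 9 = 0.9 mmHg (0.5 to 1.0 over the range of D). Against the design effect, 0.9/1.76 = 51%. With equal q in both arms, the shift is zero.

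**The case against.** The strongest reply is that handling of concomitant medication normally belongs in a full protocol or analysis plan, and that this article condenses both. That would be enough if only the analysis were missing. But the article itself fixes the success rules and describes the treatment item by its QRisk2 purpose.

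Three stronger readings are tempting, and the document does not support them.

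- A reader might infer that drugs alone carry an arm past the 20% line. That depends on the assumed variability. With an SD of change of 12 mmHg, 20.2% pass with no drugs and no exercise effect. The underlying weakness is the missing comparator; drug changes are one route through it.
- A reader might infer that the between-arm comparison is biased. Randomisation balances treatment changes in expectation unless the arms themselves alter prescribing. Support for that is thin: all arms have a 12-week programme and one measurement schedule. Participants are unblinded, and web-tool users may show activity logs to their GP, but those logs are optional and are not described as containing blood pressure readings. Comparing observed pressure regardless of treatment is also a legitimate estimand, though the article does not state it.
- A reader might take the success rules to refer to 12-month change. No time point is given. Readings within the 12 weeks raise the same issue, over less time for drug changes to accumulate.

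It is also fair that blood pressure is secondary here.

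**Conclusion.** The point stands for the within-arm rules. As written, they credit the intervention with falls caused by started or increased drugs, and the data described cannot separate the two.

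The size is modest and rests on assumptions. Drug changes in 10% of an arm add about 2 to 3 percentage points to the responder share at a 9 mmHg effect. That decides the 20% rule when ρ is 0.7, but not when it is 0.5. The 2.5 mmHg mean rule would need changes in roughly a quarter or more of the arm to be met by drugs alone.

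For the between-arm contrast the finding is conditional. A 10-point imbalance would shift it by 0.9 mmHg, about half the 1.76 mmHg design effect, but the document does not show that an imbalance is likely. The rates of drug change, their effect and the correlation are all assumed. The implied SD is systolic. The conclusion on MET-minutes is untouched.

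**What to change.** 1. Record antihypertensive drug and dose at baseline and at 12 months. Code the change blind to arm as started/increased, unchanged or reduced/stopped, and tabulate it by arm.
2. Do not count a fall of more than 10 mmHg as a response if treatment was started or increased.
3. Keep the observed between-arm comparison, regardless of treatment, as the main blood pressure analysis, and state it as such. Rest any blood pressure claim on that contrast and not on the within-arm rules alone.
4. Add one pre-specified sensitivity analysis that corrects symmetrically for starts/increases and for reductions/stops over a stated range, for example 5 to 10 mmHg.

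These steps concern measurement and analysis only and do not touch patients' treatment.

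The cost is a small extra data extraction and a somewhat lower responder proportion. Consent or record-access wording may need widening: Measures names medical-record access only for certain comorbidities and asks for no more than an indication of blood pressure treatment. Recruitment had already begun in October 2013, so any wider wording would come in part-way through.
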